#### Environment

The environment in which the camera is placed should have appropriate lighting conditions. Adequate natural light or suitable illumination can enhance image quality and recognition accuracy. The camera should be placed in a stable position to avoid image blurring. The camera's position should be adjusted to capture the patient in the frame. Ensure that the camera's field of view is unobstructed.

#### Human pose detection model

The human pose detection model (Fig. 3) will detect critical anatomical landmarks on the human body using images or videos captured by a smartphone camera. By employing a convolutional neural network (CNN) algorithm, this model can identify various joints, including the shoulder, elbow, wrist, hip, knee, and ankle. It will then generate a 3D skeletal model (Fig. 4), tracking dynamic changes in the patient's body position during motion.

**Fig. 3 Fig3:**
[figure not shown]
Human pose detection model recognizing knee flexion

**Fig. 4 Fig4:**
[figure not shown]
3D skeletal model reconstruction

When the model detects exercise postures that deviate from preset values, it will provide auditory and verbal feedback via the software to remind the patient to adjust their position based on the instructional video. Hence, the patient will receive interactive feedback during the training process.

#### Control group

Patients will be referred to the clinic weekly for 12 weeks postoperatively, during which they will receive instructions on physical therapy exercises. Every week, patients will learn the exercises at the clinic and will then be asked to take the instruction sheet home to complete the remaining exercises.

#### Compliance

To increase compliance, patients will receive adequate education on software usage before the start of the trial. Throughout the trial, patients will receive detailed instructions via handouts and reminders via texts and calls. Support will be provided to patients to answer questions throughout the trial. Compliance data will be monitored based on software usage data and patient attendance data in the clinic. The research team will collect data on patients' training frequency and duration to objectively assess participant compliance within the study.

### Outcomes

#### Clinical knee function evaluation

The estimated follow-up time was 1 day before surgery and 2, 6, 12, and 24 weeks after surgery, and the specific evaluation items included knee ROM (2, 6, 12, 24 weeks after surgery), weight-bearing progress (when fully weight bearing) and knee function and pain scores [23] (Lysholm score, Tegner score, IKDC knee subjective function score, and VAS score). At the final follow-up assessment, return-to-play (RTP) status will be evaluated based on the rehabilitation literature available for meniscus repair. **(**Table 2**)**. [4, 24, 25]

**Table 2 Tab2:** Return-to-play assessment

VAS score = 0	
IKDC score > 90	
No active effusion (Brush test negative)	
The difference in circumference between the quadriceps muscles was less than 1.5 cm	
The knee isokinetic strength test showed a ratio of bilateral quadriceps muscles greater than 90%, bilateral hamstrings greater than 90%, and unilateral hamstrings to quadriceps muscle greater than 66%	
Jump test Limb symmetry index (LSI = jump distance on the affected side/jump distance on the healthy side *100%) was greater than 90%, and the test items included a single-leg long jump test and a single-leg triple jump test	
Y-word balance test: bilateral extension asymmetry within 4 cm; bilateral comprehensive score is greater than 90%	
Lateral step-down test showed no dynamic genu valgus	

The clinical function of patients was assessed and evaluated based on IKDC and VAS score improvement via the criteria of minimal clinically important difference (MCID), patient accepted symptom state (PASS), and significant clinical benefit (SCB) [25].According to the study of Gowd et al. [25], the MCID threshold, which represents the minimal clinically important difference, is defined as an improvement of at least 10.6 points in the IKDC score after treatment or intervention. This threshold signifies that a clinically meaningful change in knee joint function is recognized. The SCB threshold, indicating significant clinical benefit, is set at an IKDC score of 27.3 points or higher after treatment or intervention. This threshold is used to confirm that the treatment has brought about a significant clinical benefit. Lastly, the threshold for patient accepted symptom state (PASS) is established at an IKDC score of 57.9 points or higher. This threshold signifies that patients subjectively consider their symptom state to be acceptable.

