**Methods:**

This study intends to enroll two groups of participants, each to be provided with informed consent before undergoing randomization into either the experimental or control group. The experimental group will undergo a digital rehabilitation program utilizing computer vision and augmented reality (AR) technology following their surgical procedure, while the control group will receive conventional care, involving in-clinic physical therapy sessions weekly. Both groups will adhere to a standardized rehabilitation protocol over a six-month duration. Follow-up assessments will be conducted at various intervals, including preoperatively, and at 2 weeks, 6 weeks, 12 weeks, and 24 weeks postoperatively. Imaging assessments and return-to-play evaluations will be conducted during the final follow-up. Clinical functionality will be assessed based on improvements in International Knee Documentation Committee (IKDC) and Visual Analog Scale (VAS) scores.

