## Methods

### Study design

This is a single-center, prospective, randomized controlled study. After receiving informed consent, participants will be randomly allocated into two groups: the experimental group and the control group will adopt the standardized rehabilitation protocol (Table 1). The experimental group will engage in a digital rehabilitation program that can be completed from home, whereas the control group will attend weekly physical therapy clinic sessions for exercise guidance. The flowchart of the study is shown in Fig. 1.

**Table 1 Tab1:** The standardized postoperative rehabilitation plan

Overall goal: Stage 1: 0–2 weeks: Control of swelling and symptoms after surgery, early progressive weight bearing, and ROM
Control of swelling and symptoms: (1) apply ice at least 3 times a day after surgery, 20 min each time; (2) apply the elastic bandage to compress the affected limb; (3) elevate the affected limb and lie flat on your back when sleeping and cushion a pillow with a certain thickness under the affected limb
ROM and brace use: (1) 0–60 degree fixation, early gentle knee movement under sitting position (2) heel support training, ensuring knee joint at 0 degrees
Weight bearing: The knee brace is secured in the fully extended knee position, and crutches are used to transition from no weight bearing to partial weight bearing as tolerated
Exercises: (1) sitting hamstring pull (2) ankle pump (3) quadriceps isometric training (4) straight leg elevation training (15–30 degrees) (5) hamstring isometric training
Overall goal: Stage 2:3–6 weeks: Early exercise and strength training, ROM, and partial weight bearing as tolerated
ROM and support use: (1) 3–4 weeks: 0–90-degree fixation, complete knee extension and bend to 90 degrees (2) 5–6 weeks 0–120-degree fixation, bend to 120 degrees
Weight bearing: With the knee brace fixed in the fully extended knee position, and using crutches, gradual weight bearing to full weight under tolerable conditions, and gradually remove of the crutches
Exercise: In addition to the training in the previous stage, include: (1) knee shin slide (2) supine straight leg raise 30 to 60 degrees (3) hip outreach training (4) lift heel stand (5) hip outreach (6) hip and (7) seat after knee flexion and stand
Overall goal: Stage 3: Weeks 7–12: Functional regression, gradual reduction of brace use, and restoration of total joint range of motion

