ROM and brace use: (1) restore full joint range of motion and (2) gradually stop brace use after full weight bearing
Exercise: Add advanced resistance training: (1) recumbent resistance straight leg raise (2) step-down training (3) heel raise training (4) knee flexion (5) straight leg draft with elastic band (6) recumbent resistance heel slide (7) forward lunge (8) half squat against wall 50 degrees (9) four-point kneeling cross stretch
Overall goal: Stage 4: Weeks 13–24: Early exercise training, full-strength recovery, cardiovascular exercise adaptation, and exercise-specific training (speed and agility training)
Exercise: Continue with the third stage of training and build on this cardiovascular endurance training (power cycling, recovery running, and jumping)
Phase 5: after return to sports assessment to determine whether to return to body contact, rotating sports

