### Subjects

Inclusion criteria:Isolated meniscus injury diagnosed by magnetic resonance imaging (MRI)Confirmation of a longitudinal tear pattern (including bucket handle tears) under arthroscopy, with a repairable tear.Suture meniscus repair with or without partial meniscectomyParticipants have sustained their meniscus injury due to physical activities, such as playing basketball.Willing to participate in this clinical trial and receive follow-up.

Exclusion criteria:Preoperative MRI diagnosis with other ligament or chondral lesions;A discoid meniscus was diagnosed under arthroscopy.Trauma and surgery to other weight-bearing joints in the lower extremities, such as torn ligaments in the ankle and necrosis of the femoral head in the hip, can indirectly affect knee load and movement.Knee osteoarthritis, defined by Kellgren–Lawrence grade II or higher or Outerbridge classification grade II and above. [19, 20]

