## Statistical analysis

Quantitative data will be analyzed using SPSS 21.0 (IBM, New York, NY, USA). The demographic, social, and preclinical characteristics of the subjects in both groups will be described. Differences in these variables between the intervention and control groups will be analyzed using either the Chi-square test or the *T* test, with continuous variables recorded as the mean and standard errors and categorical variables as rates (incidence). For continuous variables, the Shapiro‒Wilk test will be performed to verify that the variables in each group obeyed a normal distribution. For repeated measures, 2-way ANOVA analysis will be conducted. Two independent samples mean comparison *T* tests were used to compare the normally distributed continuous variables between groups. For nonparametric variables, the Kruskal‒Wallis test was used to determine the differences between the groups. Chi-square tests and Fischer exact tests were used to determine differences in categorical variables. Statistical significance was set at *p* < 0.05.

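### Knee ROM is scheduled only at postoperative visits although a preoperative visit exists, so change from the preoperative knee, a balance check and the precision gain from baseline adjustment are lost

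*Protocol article*

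**What the plan says.** The Clinical knee function evaluation section gives the visit schedule: "The estimated follow-up time was 1 day before surgery and 2, 6, 12, and 24 weeks after surgery". The abstract agrees: "Follow-up assessments will be conducted at various intervals, including preoperatively, and at 2 weeks, 6 weeks, 12 weeks, and 24 weeks postoperatively". The same sentence of the Outcomes section then lists the items to be evaluated and attaches time points to ROM: "the specific evaluation items included knee ROM (2, 6, 12, 24 weeks after surgery), weight-bearing progress (when fully weight bearing". The bracket after ROM names four postoperative visits and no preoperative one. The function and pain scores that follow in that sentence carry no such limit, and the Radiographic evaluation section places both X-ray and MRI on the day before surgery.

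Four other places bear on the point:
- Subjects, inclusion criteria: "Confirmation of a longitudinal tear pattern (including bucket handle tears) under arthroscopy, with a repairable tear".
- Table 1, Stage 3 (weeks 7 to 12) has as a rehabilitation goal to "restore full joint range of motion".
- Statistical analysis: "The demographic, social, and preclinical characteristics of the subjects in both groups will be described". ROM is not named there. Repeated measures are to be analysed by two-way ANOVA, and no baseline covariate is mentioned.
- Abstract, on how function is judged: "Clinical functionality will be assessed based on improvements in International Knee Documentation Committee (IKDC) and Visual Analog Scale (VAS) scores".

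**The concern.** ROM is the first evaluation item listed and an aim of Stages 1 to 3 in Table 1. A preoperative visit already takes place, yet as written ROM is not measured there. The week-2 value cannot stand in for a baseline, because it is taken after surgery with the allocated rehabilitation under way.

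Three things are at stake. ROM cannot be expressed as change from the patient's own preoperative state. Nobody can see whether the arms started alike on it. And the postoperative comparison gives up the precision that a prognostic covariate would bring, in a trial with only 26 to 32 patients per arm. A later analysis plan cannot repair this, because it cannot supply a value that was never measured.

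**Working it through.** **1. Is a preoperative ROM scheduled anywhere?**

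| Item | Day before surgery | Weeks 2, 6, 12, 24 |
|---|---|---|
| Visit | yes | yes |
| Knee ROM | not listed | all four listed |
| Function and pain scores | no restriction stated | no restriction stated |
| X-ray and MRI | listed | at 6 months (X-ray also 1 day after surgery) |

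The explicit list for ROM leaves out the one visit at which a baseline could be taken.

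**2. The plan's own figure.** Inputs from Sample size: d = 0.8, alpha = 0.05, power = 0.8. Sidedness is not stated, so two-sided is assumed. A two-sample t test needs 25.52, hence 26 per group, which matches the plan. Power at 26 is 0.807. This figure is not tied to ROM. It serves below only as a scale for what a baseline would be worth.

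**3. Gain from a baseline covariate.** Residual variance with adjustment = (1 − r²) × variance without it, so the standardised effect becomes d / √(1 − r²). The document gives no r. It is assumed and varied, with 26 per group:

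| Assumed r | Variance removed (r²) | Power at d = 0.8 | Difference detectable at 80% power |
|---|---|---|---|
| 0 (no baseline) | 0% | 0.807 | 0.79 SD |
| 0.2 | 4% | 0.823 | 0.78 SD |
| 0.3 | 9% | 0.843 | 0.76 SD |
| 0.5 | 25% | 0.904 | 0.69 SD |

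The single degree of freedom spent on the covariate is ignored.

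**4. Chance imbalance that would go unseen.** The standard error of the difference in mean preoperative ROM between arms, in SD units, is √(2/n).
- n = 26: √(2/26) = 0.28, and 95% of trials fall within ±1.96 × 0.277 = ±0.54 SD.
- n = 32: √(2/32) = 0.25, and the range is ±1.96 × 0.25 = ±0.49 SD.

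On the SD scale only a fraction r of an imbalance carries into the postoperative comparison. At the edge of the range for n = 26 that is 0.2 × 0.54 = 0.11 SD, 0.3 × 0.54 = 0.16 SD or 0.5 × 0.54 = 0.27 SD.

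**5. Where the gain may be smaller.** Table 1 sets brace ranges for both arms of 0–60 degrees in weeks 0–2, 0–90 in weeks 3–4 and 0–120 in weeks 5–6. Motion at the week-2 and week-6 visits may be governed partly by these shared limits, which would weaken the link to the preoperative knee. The upper part of the range for r is therefore more plausible at weeks 12 and 24.

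**The case against.** The strongest reply is that nothing in the trial's validity depends on this. The article states that "participants will be randomly allocated into two groups", so comparing postoperative ROM between arms needs no baseline, and chance imbalance is already reflected in the standard error and the p-value. Function is judged on IKDC and VAS, ROM is not a return-to-play criterion in Table 2, and no section defines change in ROM as an endpoint. The assumed r has no source in the document. All of this stands, and it limits the weight of the point.

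Several stronger readings are tempting but not supported:
- A reader might infer that the trial cannot show recovery of motion. Four postoperative measurements show its course from week 2 to week 24.
- A reader might infer that the missing baseline biases the comparison, or that an imbalance would carry over in full. Randomisation answers the first, and only the fraction r carries over.
- A reader might infer from the eligibility of bucket handle tears that preoperative ROM varies widely. The document does not say so, and tear pattern is in any case seen at arthroscopy.
- A reader might infer that the opposite knee goes unmeasured. The article does not say which side or sides are measured, which a condensed article may leave out. That knee could also be measured at a later visit.
- The Stage 3 aim of full motion is a rehabilitation goal, not an outcome definition.

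One doubt remains on the fact itself: preoperative ROM might be collected among the baseline characteristics that the Statistical analysis section mentions without listing. The explicit time points attached to ROM make this unlikely.

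**Conclusion.** The point holds in a limited form. As written, ROM has no preoperative measurement although a suitable visit exists. Change from the preoperative knee, a balance check on ROM and the benefit of baseline adjustment are given up, and none can be regained once a patient has had surgery. For an assumed r of 0.2 to 0.5 the precision loss is about 4% to 25% of residual variance, probably towards the lower end at weeks 2 and 6. The between-arm comparison of postoperative ROM remains valid, no stated figure of the plan is affected, and the IKDC and VAS conclusions are untouched. It is a minor to moderate point, worth acting on because the remedy is cheap and the loss permanent.

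**What to change.** Add ROM of the operated knee to the existing visit on the day before surgery, in both arms, with the same method and blinded assessment as at the later visits. Enter that value as a covariate in the comparisons of postoperative ROM, and show it by arm in the baseline table. If preoperative ROM is already collected, add the time point to the list in the Outcomes section; if it is left out on purpose, say why.

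The cost is a few minutes of measurement per patient, one entry in the schedule and one term in the model. It needs no extra visit and does not change the sample size. If r proves near zero, nothing is lost beyond that time and one degree of freedom.

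### SCB is defined as an attained IKDC score of 27.3, below the PASS score of 57.9, so nearly every patient qualifies, including one who got worse

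*Protocol article*

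**What the plan says.** The protocol article, under Outcomes, Clinical knee function evaluation, judges clinical function by three responder criteria. The lead-in says function is "assessed and evaluated based on IKDC and VAS score improvement via the criteria of minimal clinically important difference (MCID", and goes on to name PASS and SCB. The IKDC thresholds are then given one after another:

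- MCID "is defined as an improvement of at least 10.6 points in the IKDC score after treatment or intervention".
- SCB: "The SCB threshold, indicating significant clinical benefit, is set at an IKDC score of 27.3 points or higher after treatment or intervention".
- PASS "is established at an IKDC score of 57.9 points or higher".

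On the purpose of the SCB threshold it adds: "This threshold is used to confirm that the treatment has brought about a significant clinical benefit". The Abstract also bases the assessment of function on improvement in IKDC and VAS. Nothing elsewhere in the article restates or corrects the SCB threshold.

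**The concern.** MCID is a change from baseline, whereas SCB is worded like PASS, as a score reached after treatment. A rule that ignores the starting score cannot show that treatment produced a benefit, which is the use the article gives it. The value also puts the criteria in an impossible order: a significant benefit becomes easier to reach than an acceptable state.

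If the sentence is coded as it stands, almost every patient in both arms is likely to be an SCB responder. The trial would then report near-universal significant benefit for both programs, and the between-arm comparison on this criterion would say almost nothing. Correcting the rule after outcome data have been seen would be a post hoc change to an outcome definition.

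**Working it through.** The value 27.3 comes from a cited study, so there is no derivation in the article to reproduce. The check has a logical part, which needs no assumptions about score distributions, and a numerical part, which does.

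**Logic, from the article's own thresholds**

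1. 27.3 < 57.9, so every patient who meets PASS meets SCB. Every patient from 27.3 up to just below 57.9 also meets SCB, although the protocol treats that state as not acceptable.
2. Take a patient who goes from 45 to 30. The change is 30 − 45 = −15, so MCID fails (−15 < 10.6) and PASS fails (30 < 57.9). SCB is met (30 ≥ 27.3).
3. Read as a change, 27.3 > 10.6. Every SCB responder is then an MCID responder, and nobody who worsened can qualify.
4. The error runs one way. If IKDC scores cannot be negative (an assumption about the scale), anyone who gains at least 27.3 points also ends at 27.3 or above. The literal rule therefore keeps every change-based responder and adds others.

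**Size, under assumed distributions**

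The article gives no IKDC mean, SD, gain or correlation, so all of these inputs are assumptions. For a normal score with mean m and SD s, the share at or above a cut-off c is 1 − Φ((c − m)/s).

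| Assumed 24-week mean, SD | Share ≥ 27.3 (SCB as written) | Share ≥ 57.9 (PASS) |
|---|---|---|
| 65, 18 | 98.2% | 65% |
| 70, 15 | 99.8% | 79% |
| 75, 15 | 99.9% | 87% |
| 80, 15 | 99.98% | 93% |

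First row: (27.3 − 65)/18 = −2.09, and 1 − Φ(−2.09) = 0.982.

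Read as a change, with mean gain 25 to 40 and SD of change 16.4 to 17.7:

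- Gain 25, SD 16.4: (27.3 − 25)/16.4 = 0.14, giving 44%.
- Gain 40, SD 16.4: (27.3 − 40)/16.4 = −0.77, giving 78%.

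A wider grid used preoperative means 35 to 55, 24-week means 60 to 80, SD 12 to 18 and correlation r of 0.3 to 0.5, with SD of change = s·√(2(1 − r)):

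| Quantity | Range over the grid |
|---|---|
| SCB as written, at 24 weeks | 96.5% to 100% |
| SCB as written, already met before surgery | 67% to 99% |
| PASS at 24 weeks | 55% to 97% |
| SCB as a change | 3% to 93% |

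Within single scenarios, the excess of the literal rule over the change rule runs from 100.0 − 93.0 = 7 points (means 35 to 80, SD 12, r 0.5) to 99.7 − 3.2 = 96.5 points (means 55 to 60, SD 12, r 0.5). A mid-grid case (means 45 to 70, SD 15, r 0.5) gives 99.8 − 43.9 = about 56 points.

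**What this does to the comparison**

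The Sample size section sets a minimum of 26 per group. Even at the lowest literal rate on the grid, 26 × (1 − 0.965) = 0.9 non-responders are expected per arm. With 0 non-responders in one arm and k in the other, the two-sided Fisher p-value is 2·C(26,k)/C(52,k):

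- k = 5: 2 × 65,780 / 2,598,960 = 0.051.
- k = 6: 2 × 230,230 / 20,358,520 = 0.023.

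One arm would need at least 6 of 26 patients (23%) below 27.3, with none in the other, to reach p < 0.05.

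**The case against.** The best defence is that this is a drafting slip which any careful analyst would query. The Abstract and the lead-in both speak of improvement, the SCB sentence ends with the same phrase as the MCID sentence, and its purpose is to confirm a benefit that treatment brought about. These cues are real, but they show what was probably meant. They do not alter the rule that is written, and they support the correction.

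Several narrower points stand:

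- The improvement lead-in also covers PASS, which is an attained score, so the lead-in alone does not prove that 27.3 is a change. The ordering of the thresholds and the stated purpose carry the argument. The cited source must settle it and cannot be checked from the article.
- SCB is not named as the primary endpoint. The sample size rests on d = 0.8. The continuous IKDC and VAS analyses, MCID, PASS and the return-to-play criterion ("IKDC score > 90") are untouched.
- The rule applies equally to both arms, so it does not favour either. It inflates both rates and hides differences.
- The size of the inflation depends heavily on the assumed gain. Any single range for it is illustrative.

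**Conclusion.** The definition is wrong as written. That SCB lies below PASS, contains it, and admits patients who worsened follows from the article's own figures and needs no assumption about the score distribution.

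That nearly every patient would qualify does depend on assumed IKDC distributions. It held at 24 weeks in every scenario tried, never falling below 96.5%. The excess over a change-based rate is far less certain: 7 to 96.5 points across the wider grid. The consequence is confined to one of three responder criteria, but on that criterion the trial would overstate benefit in both arms and could hardly detect a difference between them. It should be put right before any outcome data are analysed.

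**What to change.** Check the cited source for whether 27.3 is a change or an attained score. If it is a change, replace the sentence with: SCB is an improvement of at least 27.3 IKDC points from the preoperative score. Keep PASS as an attained score, and derive MCID and SCB from change and PASS from the score at the assessed visit. The section does not say at which visit the thresholds apply, so name it in the same edit; 24 weeks, the final follow-up, is the natural choice.

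If the source does give 27.3 as an attained score, the sponsor should explain how a value below PASS can confirm significant benefit, or drop the criterion.

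The cost is one protocol sentence and the matching line of analysis code. The preoperative and follow-up IKDC scores are already planned, so no new data are needed and the sample size does not change.
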